#### 4. Assessment at Two Week Follow-Up

We will administer at two week follow-up the NRS [12], FRI [13], and the area specific instruments modified ODI [23] or NDI [24]. These questionnaires will be used to establish the short term efficacy of brief chiropractic care for spinal pain. The FABQ [19] and PCS [22] will also be administered to examine whether cognitive aspects related to the experience of pain influence pain severity, physical function and adverse events.

Also, a global measure of treatment satisfaction [27] and global measure of perceived change [35] will be administered at two week follow-up. The global measure of treatment satisfaction [27] will be used to examine the association between adverse events and treatment satisfaction. It will be measured on a five point categorical scale (very dissatisfied = 0; dissatisfied = 1; no preference = 2; satisfied = 3; very satisfied = 4). The global measure of perceived change [35] will be used to examine the association between adverse events and overall perceived change in the main complaint. It will be measured on an 11 point continuous scale varying from -5 to +5 (-5 = much worse, 0 = unchanged, +5 much better).

Blinding will be assessed at two weeks with a questionnaire [36] that asks the participants if they were in the real treatment group or the sham treatment group. The possible responses are: real treatment group; sham group; or don't know.

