### Sample Size

The sample size was based on the number needed to detect a significant difference in the primary outcome (adverse event: yes/no) between groups. We make the assumption that in the usual chiropractic group 45% of patients will experience an adverse event and that the rate in the sham group will be 25%. We believe this is a very conservative estimate given that a) the participants in the Senstad et al. study [3] had 6 treatments and there was a rate of 55% adverse events and b) that for the sham treatment previous studies have shown a mild adverse event rate of 7% [37] using the same de-tuned ultrasound method. Therefore, using a 2-sided test and alpha level of 0.05, recruiting 90 participants in each group (180 total) will provide 80% power to detect a difference this large or larger. G*Power 3.1.3 was used to calculate the sample size [38].

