#### Analysis of Secondary Outcomes

The efficacy of short term usual chiropractic care will assessed in two ways. First, for the repeated measures ANOVA will be used to compare differences between groups for the pain and physical function measures. Second, the minimum acceptable outcome [14], which involves establishing what participants consider to be a "minimum acceptable outcome" for which they would undertake a procedure. The proportion of participants meeting this target in each group will be reported descriptively and the groups will be compared by using a chi-squared test [14].

Blinding to treatment allocation will be assessed by using the Bang Index (BI) [36] which will allow us to determine if a significant proportion of participants guessed that they were in opposite treatment group. A BI value of < -0.2 indicates that significant proportion guessed wrongly, BI between 0.2 and -0.2 indicates participants guessed randomly, and BI > 0.2 indicates that the study was unblinded.

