## Discussion

To our knowledge, this is the first study to use a sham-controlled arm to examine the rate of adverse events during chiropractic care. It also appears to be the first controlled study to investigate how often adverse events occur during chiropractic care for spinal pain, as the only other controlled chiropractic study examined adverse events for chiropractic treatment of neck pain. The findings of this study will build on the limited number of previous studies conducted to examine adverse events during chiropractic care and contribute towards a more robust understanding of the safety profile of chiropractic care. In particular, the inclusion of a sham arm will enable us to better discern the rate of actual adverse events by comparing the frequency of adverse events that occurred in the usual chiropractic care group to those in the sham controlled group. This study will also provide additional evidence about the efficacy of short term usual chiropractic care for spinal pain.

There are three main limitations associated with the conduct of this study. First, we will only be able to provide two treatment sessions to each participant due to funding constraints. Consequently, in all likelihood our study will only capture the most common adverse events of chiropractic care. Second, the internal validity of this trial would have been enhanced by having the same chiropractors provide both interventions. However, we decided to use a different group of chiropractors to provide each intervention as we anticipated difficulty in recruiting sufficient chiropractors with access to both ultrasound and Activator^® ^instruments, both of which are required to administer the sham intervention. Third, the extent to which we can accurately determine the relative risk of usual chiropractic care depends on how well we are able to maintain blinding to treatment allocation. We acknowledge that it may be difficult to blind the participants with spinal pain to the assigned treatment throughout the trial and accordingly will examine blinding through administering a questionnaire. However, our findings about the success of blinding should be viewed cautiously as the questionnaire we will use to assess blinding has not been formally validated.

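### A Bang Index point value between -0.2 and 0.2 is read as random guessing without regard to sampling error, so moderate unblinding can be reported as none

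*Protocol article*

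**What the plan says.** Under Analysis of Secondary Outcomes, the protocol article sets a three-way rule on the Bang Index (BI). At the lower end, "A BI value of < -0.2 indicates that significant proportion guessed wrongly". In the middle, "BI between 0.2 and -0.2 indicates participants guessed randomly". At the upper end, "BI > 0.2 indicates that the study was unblinded". The cut-offs apply to the value of the index, and no interval or test is attached to the middle verdict. The text does not say whether one index or one per arm is classified.

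The index comes from a question asked at two weeks (Assessment at Two Week Follow-Up): "The possible responses are: real treatment group; sham group; or don't know". No expected share of 'don't know' answers is given.

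The Sample Size section plans 90 participants per arm, a number chosen for the primary adverse event outcome.

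The Discussion says that the extent to which the trial can "accurately determine the relative risk of usual chiropractic care depends on how well we are able to maintain blinding". It also asks for caution about the blinding findings, on the ground that the questionnaire has not been formally validated.

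**The concern.** An index that does not cross 0.2 means that clear unblinding has not been shown. The protocol reads it as positive evidence of random guessing. These are different statements when the index is estimated from about 90 people, because its sampling error is then of the same order as the distance from 0 to the cut-off.

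The reading matters because the adverse events are reported by participants, practitioners are not blinded, and the protocol ties the accuracy of the relative risk to how well blinding holds. If some participants know their allocation, that knowledge may affect what they report. A statement that they guessed randomly would tell readers to set this explanation aside when the data may not justify doing so.

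**Working it through.** **Inputs.** From the protocol: n = 90 per arm; band -0.2 to 0.2; three response options including 'don't know'. Assumed: share of 'don't know' answers (DK) from 0% to 50%; all 90 questionnaires returned; index calculated separately for each arm.

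**The plan's own figure.** The protocol gives no precision for the index. Its 90 per arm reproduces: for 45% against 25%, two-sided alpha 0.05 and 80% power, the normal-approximation formula gives 89 per arm, and 90 per arm gives power 0.808. The sample size is not in dispute.

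**Step 1: precision of the index.** For one arm,

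BI = (correct - wrong) / n, with 'don't know' answers counted in n

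SE = sqrt(((1 - DK) - BI²) / n)

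95% half-width = 1.96 × SE

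At BI = 0 and n = 90:

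- DK 0%: SE = sqrt(1/90) = 0.105; half-width 0.207
- DK 20%: SE = sqrt(0.8/90) = 0.094; half-width 0.185
- DK 30%: SE = sqrt(0.7/90) = 0.088; half-width 0.173
- DK 50%: SE = sqrt(0.5/90) = 0.075; half-width 0.146

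The half-width of the band is 0.2.

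**Step 2: one example.** Take an observed BI of 0.19 with DK 20%. SE = sqrt((0.8 - 0.0361)/90) = 0.0921, and the interval is 0.19 ± 0.181, that is 0.009 to 0.371. It excludes 0, yet the rule reports random guessing. With DK 0% the interval is -0.013 to 0.393, which includes 0 and is merely inconclusive. In both cases the interval reaches well past 0.2.

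**Step 3: how often the middle verdict is given.** With n = 90 the index lies in the band when correct and wrong answers differ by at most 0.2 × 90 = 18. The probability was computed exactly from the trinomial distribution with P(correct) = (1 - DK + BI)/2 and P(wrong) = (1 - DK - BI)/2. With DK 0% and true BI 0.25, for example, P(correct) = 0.625, and 36 to 54 correct answers out of 90 has probability 0.349.

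| True BI | DK 0% | DK 30% | DK 50% |
|---|---|---|---|
| 0 | 95.5% | 98.1% | 99.4% |
| 0.20 | 54% | 52% | 53% |
| 0.25 | 35% | 30% | 26% |
| 0.30 | 19% | 13% | 8% |
| 0.35 | 8% | 4% | 1% |
| 0.40 | 2.7% | 0.7% | 0.1% |

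The first row shows that false alarms are controlled. The rows for 0.25 and 0.30 show the opposite error: true values that the protocol itself would call unblinded are often labelled as random guessing.

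**Step 4: would a stricter rule work?** Suppose random guessing were concluded only when the whole 95% interval lay within -0.2 to 0.2. With a true index of exactly 0 and 90 answers, this would happen in 0%, 14%, 24%, 37% and 53% of trials at DK 0%, 20%, 30%, 40% and 50%. Perfect blinding would usually fail such a rule unless 'don't know' answers were common.

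**The case against.** The strongest reply is that nothing depends on the label. No analysis set, test or adjustment uses it, and the primary comparison and relative risk are calculated whatever it shows. This stands, and it keeps the point minor.

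Second, the Discussion already urges caution about the blinding findings. That is true, and it means the protocol does not certify blinding outright. But the reason given is the unvalidated questionnaire; sampling error is a separate matter and is not covered.

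Third, a condensed article may leave a confidence interval to the full plan. An absent interval alone would therefore be no finding. The point here is the stated verdict: adding an interval would not change a rule that calls every value in the band random guessing.

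Fourth, the band can be read as a tolerance zone in which values count as effectively random. On that reading the 0.19 example falls where the protocol intends, and it excludes 0 only if there are enough 'don't know' answers. This is fair, so the conclusion rests on Step 3, which measures the rule against the protocol's own cut of 0.2 and does not need the example.

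Fifth, any threshold misclassifies about half the time at its own boundary, and the error falls quickly beyond it. This also stands and limits the claim to true values from about 0.2 to 0.35.

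**Conclusion.** The point holds as a minor fault of interpretation. The rule turns an inconclusive point value into a positive statement of random guessing. With 90 answers, an arm with a true index of 0.25 receives that statement in about 26% to 35% of trials, and one with a true index of 0.30 in about 8% to 19%. These figures assume 50% down to 0% 'don't know' answers, full return of questionnaires, and an index calculated per arm. Missing questionnaires would widen the intervals: with 72 answers (20% missing, assumed) the half-width at 0 is 0.231 with no 'don't know' answers and 0.193 with 30%.

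A reader might infer more than this, and the document does not support it:

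- That badly failed blinding would pass. A true index of 0.40 is missed in under 3% of trials.
- That the interval is always as wide as the band. The half-widths match only when nearly everyone guesses; at 30% to 50% 'don't know' the interval's half-width is 87% to 73% of the band's (0.173/0.2 and 0.146/0.2).
- That the trial could hardly ever support a conclusion of random guessing. Step 4 shows this fails when 'don't know' answers are common.
- That the primary test is compromised. It does not use the index.

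**What to change.** Replace the middle verdict with wording such as: *The Bang Index will be reported for each arm with its 95% confidence interval. A value between -0.2 and 0.2 will be described as no clear evidence of unblinding. The relative risk of self-reported adverse events will be interpreted in light of these intervals.*

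Do not make it a decision rule that the whole interval must lie within -0.2 to 0.2, for the reason in Step 4.

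The change is to wording only. The intervals come from the counts already planned, with no added participants or data. The price is a less reassuring statement about blinding.

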### Intervention/treatment

Chiropractors will be asked to deliver one of the two study interventions. The study interventions are as follows:

1. Short term usual chiropractic care: a series of two chiropractic treatments to the spine as deemed suitable by a registered chiropractor. Treatments include one or more of the following: spinal manipulation, mobilisation, drop piece, traction, electro- therapies, ultrasound, Activator^®^, soft tissue techniques and other manual techniques offered by the chiropractor. This treatment approach replicates a common pragmatic approach in the field [1].

2. Sham Group: participants will receive two sessions of de-tuned ultrasound and de-tuned Activator^® ^treatment by a chiropractor to the regions where spinal pain is experienced. There is no known treatment benefit from the de-tuned ultrasound machine and it has been established in previous trials as a credible treatment option by patients [17,18]. Chiropractors will be directed to wind the Activator^® ^head force to minimum and then administer the force through a wooden tongue depressor at random locations in the spine near the areas of concern. The dimensions of the depressor are 19 mm wide and 150 mm long, although on average only 600 mm of the length will be in contact with the skin. This means a surface area of 1140 mm^2^. We measured the force this will provide to the skin using a force transducer. The mean of 5 measured attempts was a very low 3.7 kPa. To increase the perceived "hands on" credibility, the chiropractor will be trained to gently place one hand on an area adjacent to the participant's spine while delivering the ultrasound and Activator^® ^therapies. The four chiropractors recruited to deliver the sham treatment will be asked to administer the sham interventions as they normally use Activator^® ^tools and ultrasound and with the same enthusiasm they would use for all other therapies.

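### The blinding rule reads one Bang Index above 0.2 as an unblinded study, but the index belongs to one arm, so a credible sham can trigger the label when guesses carry no information on allocation

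*Protocol article*

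**What the plan says.** All places are in the protocol article.

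- **Analysis of Secondary Outcomes** names the Bang Index (BI) and gives three zones. Low: "A BI value of < -0.2 indicates that significant proportion guessed wrongly". Middle: "BI between 0.2 and -0.2 indicates participants guessed randomly". High: "BI > 0.2 indicates that the study was unblinded". The first two describe how people guessed; the third is a verdict on the whole trial. The section does not say which arm's value is judged or how two values of opposite sign are read.
- **Assessment at Two Week Follow-Up** asks each participant which group they think they were in. "The possible responses are: real treatment group; sham group; or don't know".
- **Intervention/treatment** relies on the sham being believable. Of de-tuned ultrasound it says that "it has been established in previous trials as a credible treatment option by patients", and it adds a light hand contact to strengthen that impression.
- **Discussion** states that "the extent to which we can accurately determine the relative risk of usual chiropractic care depends on how well we are able to maintain blinding".

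**The concern.** By definition the BI is an arm-level quantity, so two arms give two values. In the usual-care arm, guessing real is correct; in the sham arm, the same guess is incorrect. A shared belief in having had real treatment therefore appears as a positive index in one arm and a negative index in the other. That pattern is what a credible sham is meant to produce, and it says nothing about participants knowing their allocation. Applied to the usual-care arm, the written rule would call it an unblinded study.

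What is at stake is the interpretation of the primary result. The primary outcome is an adverse event that participants report themselves, and the Discussion ties confidence in the relative risk to blinding. A wrong label would lead readers to discount the relative risk for a reason the guesses do not support.

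**Working it through.** **Inputs**
- Cut-offs of -0.2 and +0.2: Analysis of Secondary Outcomes.
- Three response options: Assessment at Two Week Follow-Up.
- 90 per arm: Sample Size. All are assumed to answer the blinding question.
- Guess distributions: not in the article. They are assumed, with a range shown.

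**The plan's own figure.** The article states no BI value; the only figure used here that can be checked is 90 per group. With 45% v 25%, two-sided alpha 0.05, 80% power and no continuity correction:

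n = [1.960 x sqrt(2 x 0.35 x 0.65) + 0.842 x sqrt(0.45 x 0.55 + 0.25 x 0.75)]² / 0.20² = 88.1, rounded up to 89.

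Power with 90 per arm is 80.8%, so the stated size reproduces.

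**Formula.** Within one arm, with p_c the proportion guessing correctly and p_w the proportion guessing incorrectly (don't-knows stay in the denominator):

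BI = p_c - p_w; SE = sqrt{[p_c + p_w - (p_c - p_w)²] / n}

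**Same beliefs in both arms, 60/20/20 (54 real, 18 sham, 18 don't know of 90)**
- Usual care: (54 - 18)/90 = +0.40. SE = sqrt[(0.80 - 0.16)/90] = 0.084; 95% CI 0.235 to 0.565.
- Sham: (18 - 54)/90 = -0.40; 95% CI -0.565 to -0.235.
- The first value falls in the unblinded zone and the second in the wrongly guessed zone. The between-arm difference in guesses is zero.

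**Same beliefs in both arms, 70/20/10 (63, 18, 9 of 90)**
- Usual care +0.50 (0.33 to 0.67); sham -0.50 (-0.67 to -0.33).

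**Actual unblinding, for contrast.** With 63 correct, 18 incorrect and 9 don't know in each arm, the indices are +0.50 and +0.50. The usual-care value is the same as in the previous case; only the sham-arm value separates the two.

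**How often the rule fires when guesses carry no information.** Share of 200,000 simulated multinomial samples of 90 in which the usual-care BI exceeds 0.2:

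| Real/sham/don't know, both arms | True usual-care BI | Usual-care BI above 0.2 |
|---|---|---|
| 50/30/20 | +0.20 | 48% |
| 60/30/10 | +0.30 | 84% |
| 60/20/20 | +0.40 | 99% |
| 70/20/10 | +0.50 | above 99.9% |

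The sham arm falls below -0.2 with the same probabilities. The false label becomes likely once real guesses exceed sham guesses by more than about 20 percentage points.

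**The case against.** **The arms would be read sensibly anyway.** The index is arm-specific by definition, so both values would be calculated. The zone below -0.2 gives a sham arm that believes in its treatment its own category, and reading opposite-signed pairs might be left to a fuller document. This has some force: the plan does not ignore wrong guessing. But the article does not leave the reading open. It prints a rule whose upper zone passes judgement on the study, with no arm named and no joint reading. The complaint is about a rule that is stated, not about omitted detail.

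**A single pooled index may have been meant.** Pooling the 70/20/10 case gives (81 - 81)/180 = 0, and the false label disappears. The article does not say this, and a pooled value would not be the index it names.

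**Nothing operational depends on the label.** This stands. No analysis, exclusion or decision is tied to the BI. The Discussion makes the relative risk depend on blinding being maintained, not on this index, and asks for caution about the blinding findings because the questionnaire is not validated. That caution does not cover the reading rule.

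**The distribution is assumed.** This also stands, and it makes the result conditional.

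A reader might also infer that 0.2 lies within sampling error. The figures do not support that. Under random guessing with 90 per arm, the 95% half-width is 1.96 x sqrt(1/90) = 0.207 with no don't-knows and 1.96 x sqrt(0.8/90) = 0.185 with 20%. The cut-off is therefore at the edge of the interval or outside it, and a given arm exceeds +0.2 only about 1.4% to 2.2% of the time. The fault is in the study-level reading, not in noise around the cut-off.

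**Conclusion.** The point holds for the upper label. As written, the rule can declare a trial unblinded when participants in both arms guess alike, and can at the same time describe the sham arm as having guessed wrongly. At 90 per arm the false label appears about 48% of the time at 50/30/20 and about 99% at 60/20/20. Both figures rest on assumed guess distributions that are the same in the two arms, and on everyone answering.

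Materiality is modest. Sample size and primary analysis are untouched; what changes is what the trial may say about blinding, and so how the relative risk is interpreted.

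Two further inferences should not be drawn:
- **That blinding must also be asked earlier.** Nothing in the article makes the two-week timing an error. An early question could raise suspicion before the second treatment and the second adverse-event questionnaire.
- **That the sum of the two indices can be replaced by the between-arm difference in guessing real.** The two differ when don't-know rates differ. With usual care at 54 real, 6 sham, 30 don't know and sham at 54, 30, 6, the indices are 48/90 = +0.533 and -24/90 = -0.267. Their sum is +0.267, yet the difference in guessing real is 0.

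**What to change.** In Analysis of Secondary Outcomes:

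1. Report the BI with its 95% confidence interval separately for usual care and sham.
2. Make the labels at -0.2 and +0.2 describe guessing in that arm only.
3. Delete the sentence that turns one value above 0.2 into a verdict on the study.
4. State how the pair is read. Positive values in both arms are evidence of unblinding. A positive usual-care value with a negative sham value of similar size indicates a shared belief in real treatment. Describe other patterns with their intervals rather than forcing them into a label.
5. State that an interval including zero is not proof that blinding held.

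The cost is a few sentences. The existing questionnaire already collects what is needed, and no data collection, sample size or primary analysis changes.

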### Study Flow

A flow chart of the study is seen in Figure 1.

**Figure 1 F1:**
[figure not shown]
**Study Flow**.

## Discussion

To our knowledge, this is the first study to use a sham-controlled arm to examine the rate of adverse events during chiropractic care. It also appears to be the first controlled study to investigate how often adverse events occur during chiropractic care for spinal pain, as the only other controlled chiropractic study examined adverse events for chiropractic treatment of neck pain. The findings of this study will build on the limited number of previous studies conducted to examine adverse events during chiropractic care and contribute towards a more robust understanding of the safety profile of chiropractic care. In particular, the inclusion of a sham arm will enable us to better discern the rate of actual adverse events by comparing the frequency of adverse events that occurred in the usual chiropractic care group to those in the sham controlled group. This study will also provide additional evidence about the efficacy of short term usual chiropractic care for spinal pain.

There are three main limitations associated with the conduct of this study. First, we will only be able to provide two treatment sessions to each participant due to funding constraints. Consequently, in all likelihood our study will only capture the most common adverse events of chiropractic care. Second, the internal validity of this trial would have been enhanced by having the same chiropractors provide both interventions. However, we decided to use a different group of chiropractors to provide each intervention as we anticipated difficulty in recruiting sufficient chiropractors with access to both ultrasound and Activator^® ^instruments, both of which are required to administer the sham intervention. Third, the extent to which we can accurately determine the relative risk of usual chiropractic care depends on how well we are able to maintain blinding to treatment allocation. We acknowledge that it may be difficult to blind the participants with spinal pain to the assigned treatment throughout the trial and accordingly will examine blinding through administering a questionnaire. However, our findings about the success of blinding should be viewed cautiously as the questionnaire we will use to assess blinding has not been formally validated.

